## Abstract

**Background:**

At present, women with threatened preterm labor before 32 weeks of gestation are, after transfer to a perinatal center, treated with tocolytics and corticosteroids. Many of these women are treated unnecessarily. Fibronectin is an accurate predictor for the occurrence of preterm birth among women with threatened preterm labor. We will assess whether triage of these women with fibronectin testing, cervical length or their combination is cost-effective.

**Methods/Design:**

We will investigate a prospective cohort of women referred to a perinatal centre for spontaneous threatened preterm labor between 24 and 34 weeks with intact membranes. All women will be tested for fibronectin and cervical length. Women with a cervical length <10 mm and women with a cervical length between 10-30 mm in combination with a positive fibronectin test will be treated with tocolytics according to local protocol. Women with a cervical length between 10-30 mm in combination with a negative fibronectin test will be randomised between treatment with nifedipine (intervention) and placebo (control) for 48 hours. Women with a cervical length > 30 mm will be managed according to local protocol. Corticosteroids may be given to all women at the discretion of the attending physician. Primary outcome measure will be delivery within 7 days. Secondary outcome measures will be neonatal morbidity and mortality, complications of tocolytics, costs and health related quality of life. The analysis will be according to the intention to treat principle. We anticipate the probability on preterm birth within 7 days in the group of women with a negative fibronectine test to be 5%. Two groups of 110 women will be needed to assure that in case of non-inferiority the difference in the proportion of preterm deliveries < 7 days will be within a prespecified boundary of 7.5% (one sided test, β 0.2, α 0.05). Data obtained from women with a positive and negative fibronectin tests in both the cohort study and the trial will be integrated in a cost-effectiveness analysis that will assess economic consequences of the use of fibronectin.

**Discussion:**

This study will provide evidence for the use of fibronectin testing as safe and cost-effective method in a triage for threatened preterm labor.

**Trial registration:**

Nederlands Trial Register (NTR) number 1857, .

## Background

Preterm birth is the most frequent cause of perinatal mortality and severe perinatal morbidity in the Western world [1]. Preterm birth can be preceded by rupture of the membranes and/or by uterine contractions leading to cervical effacement and dilation. Current treatment of women with threatened preterm labor is tocolysis to diminish contractions and the administration of corticosteroids to enhance fetal lung development [2]. In the Netherlands, 7.9% of all deliveries are preterm, and 1.6% of all neonates are born before 32 weeks of gestation [3]. Women at risk for preterm birth prior to 32 weeks are transferred to a perinatal centre [4].

Discriminating those women who will deliver preterm is difficult: about half of the women treated with tocolytics and/or corticosteroids do not deliver within a short time after the occurrence of symptoms. As tocolytics and corticosteroids can cause severe side-effects in both mother and child [5-8], concerns have been expressed about overtreatment. If we are able to identify women that eventually do not deliver preterm and thus do not benefit from referral and treatment, we could prevent them from being exposed to the potential side effects of tocolytics and corticosteroids. In addition, management costs could be reduced by preventing unnecessary transport of pregnant women to perinatal centers and the associated higher treatment costs.

Fetal fibronectin is an internationally accepted predictor of preterm birth [9]. Fetal fibronectin is a glycoprotein found in amniotic fluid, placental tissue, and the extracellular substance of the decidua next to the placental intervillous space. It is thought to be released through mechanical or inflammatory mediated damage to the membranes or placenta before birth [10]. Swabs can be taken from the ectocervix or posterior vaginal fornix, and an enzyme linked immunosorbent assay (ELISA) containing FDC6 monoclonal antibody can be used to detect fetal fibronectin [11]. The results may indicate the likelihood of spontaneous preterm birth [12]. In clinical use, however, factors such as contamination of the sample with maternal blood, sampling within 24 hours after intercourse, and preeclampsia may reduce the accuracy of the test and give false positive results [13-15].

The predictive capacity of fibronectin has been the topic of previous studies. Honest and co-workers published in 2002 a systematic review on the predictive capacity of fibronectin for preterm delivery [16]. They identified 40 studies reporting on symptomatic women. The summary likelihood ratio for a positive result was 5.4 (95% CI 4.4 to 6.7) for predicting birth within 7 to 10 days of testing, with a corresponding likelihood ratio for a negative result of 0.25 (95% CI 0.20 to 0.31). Therefore fibronectin testing might be able to reduce unnecessary treatment and subsequent costs. On the other hand, introducing fibronectin tests has not yet proven to reduce health care costs if the subsequent management is subject to physicians preferences [17-21]. In addition, high false positive rates may increase health care costs in the management of low risk women.

For cervical length measurement, the situation is different. This test is shown to predict preterm delivery in asymptomatic women at 20 weeks [22]. However, the accuracy of the test is only marginally evaluated in women with symptoms of preterm labor at a later gestational age [23]. Gomez et al. evaluated the predictive accuracy of a combination of fetal fibronectin measurement and cervical length measurement [24]. In their study, 15% of the women had cervical lengths below 15 mm, and one third of these women delivered within 48 hours. Among those with a cervical length between 15 mm and 30 mm (36% of the population), 25% had a positive fibronectin test, and 15% of this group delivered within 48 hours. Of the remaining 75% of the women, less than 5% delivered within 7 days. These results are comparable with our pilot study of [name] et al. Amongst 19 women with a cervical length between 10-30 mm and a negative fibronectin test, only 1 woman delivered within 7 days[25].

At present, fibronectin testing is not routinely used in The Netherlands. To assess the risk for threatened preterm labor, only cervical length is routinely measured[2]. This measurement is frequently used as an argument to transfer and treat women for threatened preterm labor, even if clinical symptoms are mild. Identifying women that are at high risk for preterm delivery could benefit from adding fibronectin testing. Therefore we will evaluate if adding fibronectin testing to cervical length measurement is a safe and cost-effective strategy as a triage for women with threatened preterm labor.

## Methods/Design

### Aims

We will evaluate a risk assessment with fibronectin testing for women with clinical signs of threatened preterm labor. We will assess whether triage of these women with fibronectin testing, cervical length measurements or a combination is cost-effective. The results of this study can be used to support a policy of expectant management without immediate referral to a neonatal centre and without tocolysis in women with a low risk for preterm birth.

### Participants/eligibility criteria

All women between 24 and 34 weeks of gestational age with primary complaints associated with preterm labor and intact membranes will be eligible for inclusion in the study. Women with vaginal bleeding, a cerclage, cervical dilatation of more than 3 cm or previous treatment for threatened preterm labor in the current pregnancy are excluded. Other exclusion criteria are hypertension, contra indications for nifedipine and fetal distress or maternal conditions that may lead to pregnancy termination within 7 days. The study will be limited to women admitted to a perinatal centre with neonatal intensive care facilities.

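### The cohort is recruited at perinatal centres, after a referral often decided on cervical length, but its results are meant for the decision before referral; this distorts the case mix in the economic model differently for each strategy

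*Protocol article*

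**What the plan says.** **Who is studied.** Participants/eligibility criteria: "The study will be limited to women admitted to a perinatal centre with neonatal intensive care facilities". The abstract describes a "prospective cohort of women referred to a perinatal centre for spontaneous threatened preterm labor". Women above 30 mm are not excluded; both the abstract and the Procedures section give them a management path.

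**How women get there.** The Background says that cervical length is the only routine risk test in the Netherlands, and continues: "This measurement is frequently used as an argument to transfer and treat women for threatened preterm labor, even if clinical symptoms are mild".

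**What the results are for.** The Aims name a "policy of expectant management without immediate referral to a neonatal centre and without tocolysis" for low-risk women. The Economic evaluation compares five strategies that decide who is transferred and treated: everyone (I), by fibronectin (II), by cervical length (III), by the combination (IV), and sequential testing (V). It also sets the cost of testing the whole cohort against the saving from not transferring and treating low-risk women. Its inputs are cohort and trial data, plus literature on neonatal outcome by duration of pregnancy. It mentions neither data on women who were never referred nor any adjustment for how the cohort was selected.

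**The concern.** The decision to be informed is taken at the referring hospital, but the women observed are those for whom it has largely been taken already, often on one of the tests being judged. A woman with a long cervix and mild symptoms who stays at her local hospital belongs to the population of strategies I to V but does not enter the cohort.

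The model needs the share of women in each test cell: short cervix, mid-length with positive or negative fibronectin, and long cervix. If the long-cervix cell is depleted, every share with all women as denominator shifts. The shifts differ between strategies, so the comparison of strategies, which is what the economic evaluation is for, can be distorted even though each woman's data are correct.

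**Working it through.** **The plan's own figure.** The Sample size section expects 220 low-risk women from a cohort of about 660: 220/660 = 33% mid-length and fibronectin-negative. This rests on the pilot, whose total size and setting the article does not give.

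**Inputs** (Background, cited study of the combined tests):
- below 15 mm: 15%
- 15 to 30 mm: 36%, of whom 75% fibronectin-negative, so 0.36 × 0.75 = 27% of all women
- the remainder, taken as above 30 mm: 100 − 15 − 36 = 49%

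**Assumptions.**
- A fraction f of the women above 30 mm never reaches the cohort. The document does not give f.
- Selection acts only through the 30 mm cut-off.
- Cervical length alone spares women above 30 mm. The combined rule spares these plus the mid-length negatives.
- The cited study's lower cut-off is 15 mm, whereas this trial uses 10 mm.

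**Formulae.** The referred cohort has relative size D = 0.51 + 0.49(1 − f).
- Mid-length negative share of all tested: 0.27/D
- Spared by cervical length alone: 0.49(1 − f)/D
- Spared by the combined rule, against transferring all: [0.27 + 0.49(1 − f)]/D
- Yield of fibronectin within the mid-length group: 0.27/0.36

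| f | D | Mid-length negative, of all tested | Spared by cervical length alone | Spared by combined rule | Yield in mid-length women |
|---|---|---|---|---|---|
| 0 | 1.000 | 27% | 49% | 76% | 75% |
| 0.25 | 0.8775 | 31% | 42% | 73% | 75% |
| 0.50 | 0.755 | 36% | 32% | 68% | 75% |
| 0.75 | 0.6325 | 43% | 19% | 62% | 75% |

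For f = 0.50: 0.27/0.755 = 35.8%; 0.245/0.755 = 32.5% (32.45% before rounding, shown as 32%); 0.515/0.755 = 68.2%.

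**Effect on a comparison between strategies.** If every woman has a fibronectin test, the number of tests per additional woman spared, beyond cervical length alone, is 1/0.27 = 3.7 with no selection and 1/0.358 = 2.8 at f = 0.50. If only mid-length women are tested, it is 1/0.75 = 1.3 at any f. The advantage of sequential testing would therefore look smaller in the referred cohort than it is before referral.

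**The case against.** The strongest reply is that this is an applicability caveat with no demonstrated bias. Several parts of that reply stand.

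- **Direction.** A reader might infer that recruiting after referral simply inflates the benefit of fibronectin. The table contradicts this. Only the mid-length negative share over all women tested rises; the share spared by cervical length alone and by the combined rule falls, and the yield within the mid-length group does not move. The upward direction does apply to the planned comparison of whole-cohort testing cost with the saving in low-risk women, if that result is carried to all symptomatic women.
- **Size.** The fraction f is assumed. The Background says that cervical length is often, not always, the argument for transfer, and long-cervix women do enter the cohort.
- **The 33% is not corroboration.** It exceeds 27%, but the trial's lower cut-off is 10 mm and the pilot had only 19 women in this cell. If the pilot total were about 57 (an assumption, from 19/0.33), the 95% interval for 19/57 would be roughly 22% to 46%, which includes 27%.
- **Prior treatment.** Women with "previous treatment for threatened preterm labor in the current pregnancy are excluded", which might seem to sharpen the selection. If those treated before arrival tended to have short cervices, excluding them would work the other way. The document does not settle it.
- **Seven-day risk.** Selection at 30 mm alone does not change the risk of delivery within the 10–30 mm negative cell.
- **Current practice.** For overtreatment among women already transferred, the cohort is close to the right denominator. The Aims and strategy I reach further.
- **Article-level detail.** The article does not list its case record form items, and referral route may already be collected. That absence is not itself a fault. The article also plans subgroup scenario analyses, but does not tie them to referral.

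What the reply does not remove is the mismatch between the population recruited and the decision named in the Aims.

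**Conclusion.** The point holds as a mismatch of population that affects the economic model and the conclusion on referral. If women above 30 mm are under-represented, the distortion differs by strategy: upward for the incremental fibronectin share over all women tested, downward for cervical length alone and for the combined rule against transferring all, and nil for the yield of fibronectin among mid-length women. With half of the long-cervix women missing, the illustrative shifts are 27% to 36%, 49% to 32%, and 76% to 68%. They rest on an assumed referral fraction, a 15 mm lower cut-off and selection acting only at 30 mm; the true size cannot be obtained from the document.

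The document does not support a general claim that the plan overstates how many women the test reclassifies. Nor is the randomised comparison of nifedipine with placebo affected: allocation takes place within the 10–30 mm, fibronectin-negative cell.

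**What to change.** 1. Record for each woman, or confirm that it is recorded, whether she was referred or presented directly, and any cervical length measured before referral.
2. Keep the all-cohort result and add a scenario analysis to the cost model that re-weights the cervical length case mix. One simple form gives women above 30 mm a weight of 1/(1 − f) over a stated range of f, with f = 0 returning the all-cohort result. Report the ranking of strategies I to V across that range.
3. Show direct presenters as a further sensitivity analysis. They should not replace the main input: they are fewer, and nothing shows that they represent women at referring hospitals.
4. Limit the conclusion foreseen in the Aims to women already in a perinatal centre, unless the ranking of strategies holds across the range.

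The cost is two baseline data fields, some extra modelling, and a more cautious conclusion with wider uncertainty. The cost model is still to be developed, according to the Economic evaluation, and neither the randomised design nor its sample size changes.

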### Procedures, recruitment, randomisation and collection of baseline data

Women meeting the eligibility criteria will be informed and invited to participate in the study and asked for written informed consent. At study entry baseline demographics, obstetric and medical history will be recorded. Before cervical length measurement, women will be tested for fibronectin. Therefore a sample of cervicovaginal secretion will be taken by rotating a swab in the posterior vaginal fornix for 10 seconds. Analysis will be performed using the FullTerm TLi_IQ _system of Hologic [26].

Women with a cervical length below 10 mm and women with a cervical length between 10-30 mm in combination with a positive fibronectin test will be treated with tocolysis. These women are considered to be at high risk for preterm delivery. Women with a cervical length above 30 mm will be treated according to the discretion of the physician. Women with a cervical length between 10-30 mm and a negative fibronectin test are considered to be at low risk, they will enter a double blind trial in which they will be randomised by a central web-based system between tocolytics or placebo (1:1). Details of delivery and maternal assessments during pregnancy of all women are recorded in case record forms (CRF) that are accessible through a closed part of a central website. All data will be collected, coded and processed with adequate precautions to ensure patient confidentiality.

### Interventions

All high risk women will receive tocolytics according to local protocol. Fibronectin negative women with a cervical length between 10-30 mm will be randomly allocated to tocolytics or placebo (figure 1). Active treatment will be performed with the calcium channel blocking agent nifedipine with a total daily dose between 80 and 120 milligrams for 48 hours. Active drug and placebo will be administered orally at the same volume and rate. Corticosteroids will be administered at the discretion of the attending physician.

**Figure 1 F1:**
[figure not shown]
**Flow chart APOSTEL-I study, an overview of which patients in the APOSTEL-I cohort will be randomized based on their cervical length and fibronectin status**.

Progression of labor will be monitored every 12 hours by means of clinical observation and/or vaginal examinations for 48 hours. If labor seems inevitable in that period, study medication can be stopped and another tocolytic (excluding nifedipine) may be administered.

### Follow up of women and infants

Details of admission of newborns to the neonatal intensive care unit and neonatal complications will be recorded. Long term follow up is not part of this study.

### Outcome measures

The primary outcome measure is number of days to delivery truncated at 7 days after study entry. Secondary endpoints are neonatal mortality, neonatal morbidity, maternal morbidity (side effects of nifedipine), costs and health related quality of life.

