#### Data analysis

The results of the randomised trial will be analyzed according to the intention to treat principle. We will analyze costs and effects of a strategy based on fibronectin measurement and cervical length, in which only fibronectin positive women will be transferred to a perinatal center and/or and treated. Costs and effects of this strategy will be compared to a strategy in which these women will be transferred and treated merely based on a clinical diagnosis by e.g. vaginal examination and/or cervical length measurement.

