In our cohort, we will obtain data on the moment of delivery in women treated with tocolytics and not treated with tocolytics. In addition to our cohort data, we will obtain data from medical literature on the occurrence of neonatal mortality and morbidity in relation to duration of pregnancy, both with and without treatment of corticosteroids. We will use this to calculate the expected neonatal mortality and morbidity for each of the five strategies mentioned above.

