## Discussion

In women with clinical signs of threatened preterm labor, fibronectin can discriminate between those at low risk and high risk for immediate preterm delivery. Since treatment of low risk women might be unnecessary, testing for fibronectin is thought to be a cost effective strategy. It may protect mother and fetus from possible side effects of tocolytics and corticosteroids, lessen burden of perinatal centers and decrease stress and anxiety for the families. So far, no randomised trial has shown beneficial effects of fibronectin testing for women presenting with threatened preterm labor, despite its high negative predictive value. Although the use of fibronectin tests for these women is already implemented in some clinics and even incorporated into guidelines [27], neither its safety as a triage instrument, nor its cost effectiveness has been established.

We decided to use a fixed protocol to translate the test results into a management strategy with nifedipine, to out rule the influence of individual physicians. Nifedipine has not yet been tested against placebo as a tocolytic drug, though both the Cochrane Collaboration [28] and the Dutch Society of Obstetrics and Gynaecology [2] recommend calcium antagonists as first choice. It is unlikely that using another tocolytic drug would lead to different outcomes of this trial, since fibronectin negative women have a low a priori probability of delivering within 7 days after the test. So even though we randomize on therapy level, this trial will evaluate fibronectin testing and cervical length measurement for women with threatened preterm labor.

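### The only mortality endpoint is neonatal, so a fetal or intrapartum death after randomisation counts as an adverse result in no named infant endpoint

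*Protocol article*

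**What the plan says.** The Outcome measures section lists, after the primary outcome: "Secondary endpoints are neonatal mortality, neonatal morbidity, maternal morbidity (side effects of nifedipine), costs and health related quality of life". The Methods/Design part of the abstract agrees: "Secondary outcome measures will be neonatal morbidity and mortality, complications of tocolytics, costs and health related quality of life". Fetal death, stillbirth and intrapartum death are named in neither list, nor as an endpoint anywhere else in the article.

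The primary outcome is the time to delivery, cut off at day 7. It takes no account of whether the child is born alive.

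On data collection, Follow up of women and infants says: "Details of admission of newborns to the neonatal intensive care unit and neonatal complications will be recorded". The Procedures section is wider: "Details of delivery and maternal assessments during pregnancy of all women are recorded in case record forms (CRF". On the analysis set there is one rule, in Data analysis: "The results of the randomised trial will be analyzed according to the intention to treat principle". No denominator is given for neonatal mortality or neonatal morbidity.

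The rationale uses a wider frame. Background opens with "Preterm birth is the most frequent cause of perinatal mortality and severe perinatal morbidity in the Western world", and Discussion says of fibronectin testing: "It may protect mother and fetus from possible side effects of tocolytics and corticosteroids".

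**The concern.** Randomised treatment starts while the child is still a fetus, from 24 weeks, and one arm receives placebo instead of nifedipine. A death before or during birth is therefore a post-randomisation outcome that either arm could produce. An endpoint that begins at live birth selects on something that happens after randomisation and leaves out the most severe infant outcome.

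The article presents the trial as evidence that the triage is safe. If fetal deaths occurred unequally between the arms, the infant endpoints as named would not show it. The reader of the results would see a comparison of infant harm that omits part of that harm.

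**Working it through.** **The plan's own figure.** The article states no rate or sample size for the infant endpoints. Its one design figure is 110 women per arm for the primary comparison (5% in both arms, margin 7.5 percentage points, one-sided alpha 0.05, power 80%). The usual formula with unpooled variance gives

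n = (1.645 + 0.842)² × 2 × 0.05 × 0.95 / 0.075² = 104.4, rounded up to 105 per arm.

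At 110 per arm the same formula gives 81.8% power, so the stated size is slightly conservative. Nothing below depends on it except the denominator of 110.

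**Tracing one case.** Take a randomised woman whose fetus dies in utero or in labour.

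| Named endpoint | How the case enters |
|---|---|
| Primary outcome, delivery by day 7 | As a delivery, like any other |
| Primary outcome, delivery after day 7 | Same value as an uneventful ongoing pregnancy |
| Neonatal mortality | No event |
| Neonatal morbidity | No event; denominator not stated |

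**Frequency.** The documents give no fetal death rate. I assume 0.2% to 2% and one fetus per woman, 220 women in all. Expected deaths are 220 × p, and the chance of at least one is 1 − (1 − p)^220.

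| Assumed p | Expected deaths, both arms | Chance of at least one |
|---|---|---|
| 0.2% | 0.44 | 36% |
| 0.5% | 1.1 | 67% |
| 1% | 2.2 | 89% |
| 2% | 4.4 | 99% |

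**Effect on the reported figures.** Take an arm of 110 with no neonatal deaths, an assumed 10 morbidity cases, and 1, 2 or 3 fetal deaths.

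| Fetal deaths | Neonatal mortality | Fetal plus neonatal death | Morbidity, all 110 | Morbidity, live-born | Death or morbidity, all 110 |
|---|---|---|---|---|---|
| 1 | 0% | 1/110 = 0.91% | 10/110 = 9.09% | 10/109 = 9.17% | 11/110 = 10.00% |
| 2 | 0% | 2/110 = 1.82% | 9.09% | 10/108 = 9.26% | 12/110 = 10.91% |
| 3 | 0% | 3/110 = 2.73% | 9.09% | 10/107 = 9.35% | 13/110 = 11.82% |

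With all randomised as denominator, the dead fetus counts as free of morbidity. With live births as denominator, it is removed. The live-born rate then moves by 0.08 to 0.26 percentage point, only because the denominator shrinks. In neither case is the death an event. The uncounted deaths are the main matter; the choice of morbidity denominator has little effect.

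**The case against.** The strongest reply is that this is a condensed article. It lists the secondary endpoints in one sentence and defines none of them. A full protocol might define mortality more widely or report fetal deaths as serious adverse events. That would rightly dispose of a complaint about missing detail. It does not dispose of this one, which concerns the event chosen: the abstract and Outcome measures both say neonatal, and neither names a wider event.

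The rationale is also weaker support than it looks. The Background sentence is general epidemiology, and the Discussion sentence speaks of side effects, not death. Neither contradicts the endpoint list. The case rests on exposure before birth and on the claim of safety.

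A reader might infer more than the text allows on four points.

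- *Such a fetus drops out of the morbidity denominator.* No denominator is stated. Intention to treat could equally mean that all randomised are counted.
- *The trial's mortality definition feeds the cost-effectiveness model.* Economic evaluation does say "We will use this to calculate the expected neonatal mortality and morbidity for each of the five strategies mentioned above", but its mortality and morbidity inputs come from the literature by duration of pregnancy, and the cohort supplies the time of delivery. A stillbirth in the trial is not a mortality input there.
- *Stillbirths are lost to the trial.* Delivery details are recorded for all women, so these cases may well be on file. They enter no named mortality endpoint.
- *The reported mortality will be seriously wrong.* One can construct an arm with 1 neonatal and 2 fetal deaths, reported as 1/108 (0.9%) instead of 3/110 (2.7%). That rests on invented counts and an unstated denominator, in a stratum considered at low risk, with fetal distress excluded at entry.

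**Conclusion.** The point holds as a choice of endpoint that should be changed. As named, the infant endpoints contain no fetal or intrapartum death. The primary outcome sees such a case only as a delivery, or not at all after day 7. Under either plausible morbidity denominator the death is not counted against the arm.

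The size is limited. It concerns secondary endpoints with few expected events: by assumption, 0.44 to 4.4 fetal deaths in the whole trial, each 0.9 percentage point of an arm of 110 if all pregnancies are singletons. The primary outcome, the sample size and the interim analysis do not change. It would go too far to say that the safety conclusion rests on this count, because non-inferiority is tested on delivery within 7 days. The infant comparison that accompanies that test would nevertheless be incomplete.

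**What to change.** In the abstract (Methods/Design) and in Outcome measures:

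- Replace neonatal mortality by perinatal mortality, defined as fetal death after randomisation plus neonatal death. Use all fetuses of randomised women as denominator; the eligibility section does not exclude multiple pregnancies.
- Keep neonatal morbidity, and add the composite of perinatal death or neonatal morbidity with the same denominator, so that a death cannot pass as absence of morbidity.

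The Economic evaluation section is outside this change. Widening mortality there would need different literature inputs, not only another word.

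The cost is small. Deaths unrelated to treatment add a little noise. The sponsor must confirm that vital status at birth is part of the delivery details in the case record form, since the article does not list it. If multiple pregnancies are enrolled, the analysis must allow for fetuses of the same woman not being independent.
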